### Screening logs

Screening logs are maintained by each participating center to record: the patients admitted to the neurosurgical unit with any traumatic ICH; whether they are eligible for the trial or not and whether they are recruited or not (and if not, why not, if the reason can be ascertained). These will be used to provide a context for the study, to monitor recruitment rates, and as the basis for constructing the CONSORT diagram for reporting the trial.

### Center eligibility

The centers recruited are those already collaborating successfully with the team in other studies (STICH, STICH II, RescueICP) plus those identified by the various networks: TARN (Trauma Audit and Research Network), EBIC (European Brain Injury Consortium) and EMN (Euroacademia Multidisciplinaria Neurotraumatologica), BrainIT, EANS (European Association of Neurosurgical Societies), GNAMED (Scottish and Newcastle Neurosurgery Research Group), SBNS (Society of British Neurological Surgeons), and BNRG (British Neurosurgery Research Group).

Only centers that can demonstrate effective trial experience and previous adherence to trial guidelines with high follow-up rates are eligible to take part. In order to be eligible a center must be able to recruit a minimum of one patient per year. They must be able to communicate with the research team. (At least one member of the local team must be proficient in English and provide contact details where they can be reached easily to support the local center and respond to the trial management team in Newcastle.) They must be able to provide CT scans of sufficient quality to the study centre in Newcastle. They must be able to arrange follow-up for patients with limited literacy.

Each center is required to obtain ethical approval and other permissions as needed to conform with local and national legislation and research governance frameworks and to provide documentary evidence to the trial management team that these permissions are in place, prior to site registration and initiation. Each site is also required to sign an agreement with the sponsor (Newcastle upon Tyne Hospitals NHS Foundation Trust) and the contractor (Newcastle University). Applications by the lead collaborator in each center for ethical approval (or SSA in the UK) are supported by the trial manager and the clinical lead for the center and country in which the center is located. Also within the UK, R&D approval is sought in respect of all participating centers and the study is open to audit (‘for cause’ or as part of the routine 10% check) by the appropriate research governance teams in the participating Trusts. A member of the study team visits centers with high volume recruitment or where there are concerns about patient eligibility (identified by central monitoring) to confirm patient existence and monitor adherence to the trial protocol, against pre-determined, risk-based criteria (we do not anticipate conducting 100% site data verification).

### Approval to start

MREC approval for the study was obtained from Southampton Multicentre Research Ethics Committee. Appropriate local ethical approval is sought from each participating center in the study with proof of the approval forwarded to the trial coordinating office before recruitment can be started. The trial is conducted according to local ethical and Research and Development procedures. An agreement is signed between the sponsor (Newcastle upon Tyne NHS Hospitals Foundation Trust), the holder of the study funding (Newcastle University) and the hospital center prior to commencing the study at the center.

### Patient recruitment

All appropriate patients who are considered for STITCH(TRAUMA) must have a CT scan to confirm the diagnosis and the size and location of the hematoma. Any clotting or coagulation problems must be corrected prior to randomization in line with standard clinical practice.

#### Inclusion criteria

• Adults aged 14 years or over

• Evidence of a TICH on CT with a confluent volume of attenuation significantly raised above that of the background white and grey matter that has a total volume >10 mL calculated by (width × height × length)/2 in cm

• Within 48 h of head injury

• Clinical equipoise: only patients for whom the responsible neurosurgeon is uncertain about the benefits of either treatment are eligible

#### Exclusion criteria

• A significant surface hematoma (EDH or SDH) requiring surgery (the indications for intervention for these patients are already very well defined)

• Three or more separate hematomas fulfilling inclusion criteria

• If the hemorrhage/contusion is located in the cerebellum

• If surgery cannot be performed within 12 h of randomization

• Severe pre-existing physical or mental disability or severe co-morbidity which would lead to a poor outcome even if the patient made a full recovery from the head injury (examples would be a high level of dependence before the injury or severe irreversible associated injury such as complete spinal cord injury)

• Permanent residence outside a study country preventing follow-up

• Patient and/or relative has a strong preference for one treatment modality

There is no specified upper age limit. The need for clinical equipoise and explicit exclusion of patients with severe pre-existing physical or mental disability or severe co-morbidity which might lead to a poor outcome even if the patient made a good recovery from the head injury excludes the older less able patient while allowing a fit older person to be included. Hematoma rates are known to be more common in the older head-injured patient.

#### Consent procedure

Written witnessed informed consent of the patient or relative must be obtained by trained neurosurgical staff prior to randomization. The member of neurosurgical staff provides a written information sheet and allows as much time as possible to discuss the options. One copy of the consent form is given to the patient, one is filed in the patient notes, and one is filed with the trial documentation. If the patient is unable to give consent themselves due to the nature of the hemorrhage a personal representative is approached to give consent on behalf of the patient. The personal representative is the person with a close personal relationship with the patient who is themselves capable and willing to consent on behalf of the patient. (If the patient is unable to consent and the closest relative is not available the patient cannot be included in the study.)*

*** In Scotland, if proxy consent is necessary this should be obtained from the welfare guardian or, if there is none, from the nearest relative.

### Randomization (treatment allocation)

Before randomization, a one-page form is completed by the responsible neurosurgeon recording demographic (age, gender) and TICH characteristics (site, side, ABC measures to define volume) and status at randomization (pupils equal and reacting or not). The clinician either telephones the independent 24-h telephone randomization service or accesses the randomization website and enters the randomization information. At the end of the randomization phone call/web data entry process the neurosurgeon is informed of the patient identifier number for the trial and the treatment group the patient is allocated to. The neurosurgeon records this information on the randomization form and then faxes the form to the STITCH(TRAUMA) Office. If the site has problems contacting the randomization service they are able to contact a member of the project team using the study backup number.

The data manager checks this information against the information received from the randomization center and enters the data into an anonymized password protected database. A list of patient names and study numbers are kept in a separate file to ensure patient confidentiality is maintained.

Allocation is stratified by geographic region, with a minimization algorithm based on age group and severity (as measured by whether the pupils are equal and reacting or not) and with a random component (that is, with probability of 80%).

### Trial interventions

The two trial interventions are: (1) early evacuation of the hematoma by a method of the surgeon’s choice (within 12 h of randomization), combined with appropriate best medical treatment; or (2) best medical treatment combined with delayed (>12 h after randomization) evacuation if it becomes appropriate later. Both groups are monitored according to standard neurosurgical practice.

If the patient is randomized to early surgery this should be undertaken as soon as possible and within 12 h of randomization.

Best medical treatment may include (depending on the practices within the center) monitoring of ICP or other modalities and management of metabolism, sodium osmotic pressure, temperature, and blood gasses.

All patients also have an additional CT scan at about 5 days (+/−2 days) to assess changes in the hematoma size with and without surgery. This will enable us to demonstrate the proportion of the clot removed by surgery or the changes in volume of the clot without surgery.

### Compliance

Patients or their relatives may withdraw consent for an operation, or conversely request an operation after randomization, thereby leading to crossover between the arms. These are rare events but in surgical trials it is common for the patient’s condition to change over time and a patient randomized to initial conservative treatment may deteriorate and require surgery later. Such crossovers and the reasons for them are documented. Information is collected about the status (GCS and focal signs) of patients through the first 5 days of their trial progress and ICP/CPP measures in invasively monitored patients in order to be able to describe the change in status that leads to a change in equipoise for the treating neurosurgeon, and subsequent surgery in patients initially randomized to conservative treatment.

Compliance with treatment allocation is monitored by the data manager.

In surgical trials patients allocated to the non-surgical arm of the trial may later deteriorate and surgeons may intervene. This was the case in the MRC-funded STICH trial
[3], in trials of cardiac surgery compared with angioplasty, in the MRC-funded back pain trial
[10] and in the SPORT trials
[11]. These crossover rates to surgery were 26%, 28%, 28%, and 30%, respectively. While surgical trials will always have such crossovers when surgeons perceive that there is value in operating on patients who deteriorate after initial randomization into the conservative limb of the trial, we must understand, monitor, and report the rates of such crossovers.

The aim is to achieve as high compliance as possible but experience and the above literature suggest that it is neither practical nor ethical to have 100% compliance with conservative treatment. During the recruitment of centers and at investigator meetings the importance of clinical equipoise and minimizing crossovers is emphasized and any crossover occurring within 12 h of randomization is investigated. Centers exhibiting high crossover rates may be withdrawn from the study.

### Data collection

To preserve confidentiality all patients are allocated a unique study identifier during the randomization process which is used on all data collection forms and questionnaires. Only a limited number of members of the research team are able to link this identifier to patient identifiable details. This is necessary in order to carry out centralized follow-up.

All study documentation is held in secure offices and the study research team operate to a signed code of confidentiality. All data are entered into an anonymized password-protected database by the data manager. Paper copies of questionnaires are kept in locked cabinets in a locked room.

Any previously collected data are retained for patients who subsequently withdraw from the trial. This data is anonymized and kept confidential.

Trial documentation will be kept for 15 years after publication of the final paper/report from this study.

#### Randomization form

This provides baseline information and is required in order to randomize the patient.

#### Two-week/discharge form

At 2 weeks after randomization or at discharge or death (whichever occurs first) the discharge/2-week form is completed by the responsible neurosurgeon or research nurse. This form records the date, the event that triggers the form, and the patient’s status at that time, whether the patient has had surgery (and why if randomized to initial conservative treatment or why not if randomized to early surgery), the patient’s GCS and localizing features for the 5 days following randomization, the occurrence of any adverse events (including death, pulmonary embolism, deep vein thrombosis, surgical site infection) following randomization, past medical history, and status prior to the ictus. This form together with copies of the randomization CT scan and the 5-day post-randomization CT scan (as detailed below) should be sent to the STITCH(Trauma) office at the Neurosurgical Trials Unit in Newcastle UK within 2 weeks. The data manager enters the data into the anonymized password-protected database.

#### CT scans

Copies of two CT scans are required: the diagnostic CT scan prior to randomization and a 5-day scan. All patients have undergone a diagnostic CT scan as standard practice. The 5-day scan is performed between 3 and 7 days after randomization. Many patients receive this as part of standard treatment and the study accepts and uses any scan taken for clinical purposes during this period. Only patients who do not receive such a scan during this period require an additional scan.

The preferred scan is a CT scan with volume acquisition 32 × 0.5 mm (or equivalent); 120 Kv 400 mA (or equivalent); 220 FOV. The angle should be parallel with the anterior cranial fossa, coverage from base of skull to vertex; reconstruct 5 mm whole head, soft tissue filter.

The preferred method of sending CT scans is in DICOM compatible format. DICOM images (on separate CDs for the two time points) are sent anonymized with patient identifier. They are checked by the data manager initially on receipt at the STITCH(Trauma) office to ensure that the hematoma characteristics at randomization conform to the required inclusion criteria. Where protocol deviations are suspected the data manager arranges for the scan to be viewed by a trained reader immediately and if their suspicions are confirmed the center is contacted immediately to prevent repetitions.

The data manager loads the scans into a specialized password-protected scan management program. The scans are then allocated a separate randomly created identifier by the data manager, so that it is not possible for the reader to identify the before and after scans of the same patient. The scans are stored in locked cabinets. A separate list identifying patient identifier and scan identifier is kept by the data manager.

The CT scans are analyzed subsequently by trained readers using the scan management program. Their passwords only give access to scans blinded to treatment group and patient identity following a defined protocol.

#### Follow-up

Postal follow-up occurs at 6 and 12 months using questionnaires translated into the appropriate language. The patient’s GP (in the UK) or consultant (outside the UK) is contacted at 4.5 months to check that the patient is alive and to confirm his/her place of residence. At this time the GP/Consultant is also requested to complete a major adverse events form. The 6-month outcome questionnaire is mailed to the patient at 5 months for completion by the patient or relative if the patient is unable to complete it themselves. If necessary a reminder is sent at 6 months and telephone follow-up at 7 months by ‘blinded’ clerical or nursing staff to enhance response rates. In countries where the postal system is poor, patients are requested to attend a follow-up clinic at which the questionnaire is distributed and collected. In countries where literacy or language/dialect are problematic a ‘blinded’ interviewer administers the questionnaire. This methodology has been used to good effect in previous studies: STICH and STICH II.

The costs associated with surgical treatment (theater time, consumables, overheads) will be collected from published resources and local cost surveys undertaken by the study health economist. Length of stay, healthcare resource use outside of hospital, together with productivity costs arising from absence from work, and additional costs for family members through extra caring responsibilities are collected using the additional 3-month postal questionnaire and extended 6-month and 12-month postal questionnaires in the UK. Consequences will be measured by combining data on quality of life with survival to generate Quality Adjusted Life Years. This will include measurement of healthcare costs, quality of life (EQ-5D), work absence (WHO Health and Performance Questionnaire-Clinical Trial Version), and carer activities (measured by Discrete Choice Experiment developed by HERU). EQ-5D and survival are collected for all patients by the postal outcome questionnaires in order to generate QALYS for the whole study and for a UK-only analysis (Figure
1).

**Figure 1 F1:**
[figure not shown]
Chart showing study timetable for treatment of patients.

### Serious adverse events

Serious adverse events (SAEs) are recorded on the Major Adverse Events form. Serious adverse events are adverse experiences that result in any of the following outcomes: death; life-threatening events; requirement for inpatient hospitalization or prolongation of existing hospitalization; or persistent or significant disability or incapacity.

All SAEs should be reported to the STITCH Office within 7 days of the local investigator becoming aware of the event and to the local ethics committee or other regulatory bodies as required.

### Outcome measures

Primary: Unfavorable outcome will be death or severe disability which will be defined using a prognosis based eight-point Glasgow Outcome Scale/ Modified Rankin Scale
[3,12].

Secondary: Rankin, EQ-5D, Mortality, Survival, Major Adverse Events (death, pulmonary embolism or deep vein thrombosis, infection, re-hemorrhage), QALYs, total healthcare costs, social costs.

The Glasgow Outcome Scale is the specific measure for head injury and the eight-point scale provides more sensitivity than the five-point scale. For patients with a very poor prognosis an outcome of good recovery, moderate disability or upper severe disability would be regarded as a favorable outcome. For patients with a better prognosis favorable outcome would be good recovery or moderate disability. A structured postal version has been developed
[13]. The Rankin scale is widely used as a functional outcome measure in stroke and allows comparison of results between this study of patients with traumatic ICH and studies of patients with spontaneous ICH. EQ-5D is the standard measure of quality of life incorporating a utility value and has been developed in many languages.

### Sample size

Previous studies have suggested a favorable outcome in the non-operated group of about 40% and a favorable outcome in the surgical group of about 60% to 70%. However this was in observational studies. Assuming a favorable outcome (good recovery or moderate disability on the Glasgow Outcome Scale) of 50% from conservative treatment a total sample size of 776 would be required to show a 10% benefit (that is, 50% *vs.* 60%) from surgery (2p <0.05) with 80% power. A safety margin of 9.5% is built in to allow for loss to follow-up making a total sample size of 840 to be recruited and randomized (420 per arm).

In order to achieve this sample size in a reasonable time span and to provide robust evidence it is necessary to recruit patients from outside UK. In England and Wales there are only 30 neurosurgical units and only one-third of these participate in randomized controlled trials. Experience with interested neurosurgical centers in previous studies has shown that about 25% of recruited centers fail to recruit any patients and a further 25% only recruit one or two patients. The best recruiting centers will recruit about 10 patients per year so to complete patient recruitment within the timescale we will approach at least 150 centers.

Loss to follow-up is kept as low as possible. In the STICH study the loss was about 5%. In STITCH(TRAUMA) the population is a little younger and likely to be more mobile; however, we carry out more checks and implement procedures that we have developed to minimize loss to follow-up. Methods of follow-up are adapted to those most likely to be successful within each country and center according to local population and care characteristics. Centers that achieve poor follow-up are monitored closely and may be withdrawn from the study if they are unable to locate patients for 6-month follow-up. We require residence in any study country as an eligibility criterion so patients who suffer a head injury whilst on holiday and might be lost to follow-up are not eligible and are not included.

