### Statistical analysis

Analysis will be on an ‘intention-to-treat’ basis. The primary analysis will be a simple categorical frequency comparison using the uncorrected chi-squared test for prognosis-based
[13,14] favorable and unfavorable outcomes at 6 months. Patients with a good prognosis will be categorized as having a favorable outcome if they achieve good recovery or moderate disability on the Glasgow Outcome Scale. Patients with a poor prognosis will be categorized as having a favorable outcome if they achieve good recovery, moderate disability, or upper severe disability on the extended Glasgow Outcome Scale. Logistic regression analysis will be undertaken to adjust for covariates. Secondary outcomes will also be analyzed using the prognosis based method as specified in STICH
[3].

Given the likelihood of a proportion of crossovers, a secondary sensitivity analysis of per-treatment as well as an analysis considering crossovers to surgery as failed medical treatment will be undertaken. Further analyses of factors that drive crossovers as well as per-protocol and per-treatment analyses will be conducted to investigate the effect of crossovers.

Any subgroup analyses will be based on tests of interaction. The predefined subgroups (all of which will be considered exploratory, since the study is not powered for formal subgroup analyses) include the following: age; hematoma volume; Glasgow Coma Score; time from injury to randomization; severity of neurological deficit; pupils equal and reacting or not; planned method of hematoma removal; patients with invasive monitoring (ICP/CPP); anticoagulation status.

Interim analyses are conducted at intervals predetermined by the DMEC. The results of interim analyses are strictly confidential and the trial will only be stopped early if one or other treatment policy shows an advantage at a very high significance level, or if recruitment rates are unexpectedly low.

Deterministic and probabilistic sensitivity analyses will be conducted to consider the importance of individual parameters and assumptions in determining cost-effectiveness. This will include the effect of time horizon, variation in unit costs across centers, and quality of life values. Bootstrapped-generated differences in costs and effectiveness between strategies will be computed, and results presented using cost-effectiveness acceptability curves (CEACs).

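### The 9.5% loss-to-follow-up margin does not lead from 776 to 840: the margin built in is 64 patients, 8.2% of 776 or 7.6% of 840 (minor)

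*Protocol article*

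**What the plan says.** All the figures stand in consecutive sentences of the protocol article, section Sample size.

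- Control rate: "Assuming a favorable outcome (good recovery or moderate disability on the Glasgow Outcome Scale) of 50% from conservative treatment".
- Required number: "a total sample size of 776 would be required to show a 10% benefit", specified as 50% against 60%.
- Error rates: "from surgery (2p <0.05) with 80% power".
- Allowance: "A safety margin of 9.5% is built in to allow for loss to follow-up making a total sample size of 840", with 420 per arm.

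The same section reports a loss of about 5% in the group's earlier trial of spontaneous haemorrhage. It describes the present population as a little younger and probably more mobile, and lists extra measures to limit loss. It gives no rounding or other step between 776 and 840.

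The section Statistical analysis names the primary test: "a simple categorical frequency comparison using the uncorrected chi-squared test". The section Blinding says the intention-to-treat analysis takes in randomized patients whose outcome can be collected, so each patient lost reduces the number in the primary comparison.

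**The concern.** The section gives a starting number, a percentage and an end number, and presents the third as the result of the other two. The three do not agree. 840 lies below both totals that a 9.5% allowance can produce, so the gap is not rounding up.

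What is at stake is the accuracy of the stated allowance. A reader would take it that about 80 lost patients (9.5% of 840) are covered. The number that leaves the required 776 intact is 64.

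**Working it through.** **Inputs.** Sample size section: favorable outcome 50% and 60%; two-sided 0.05; power 80%; 776 required; 9.5% margin; 840 randomized, 420 per arm; about 5% loss in the earlier trial. Statistical analysis section: uncorrected chi-squared test.

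**1. Reproduce 776.** Pooled-variance formula, no continuity correction, with mean rate 0.55:

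n per arm = [1.960 × √(2 × 0.55 × 0.45) + 0.8416 × √(0.5 × 0.5 + 0.6 × 0.4)]² / 0.10²

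= [1.960 × 0.7036 + 0.8416 × 0.7000]² / 0.01 = 387.3, so 388 per arm and 776 in total. The plan's figure is exact. The arcsine formula also gives 776.

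**2. Forward from 776 with 9.5%.**
- Added to the evaluable number: 776 × 1.095 = 849.7, so 850.
- Allowing for a 9.5% loss: 776/0.905 = 857.5, so 858 (429 per arm).

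**3. Backward from 840 with 9.5%.**
- 840 × 0.905 = 760.2.
- 840/1.095 = 767.1.

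Neither is 776.

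**4. Other starting numbers.** The unpooled formula gives 770, which a 9.5% margin takes to 844 or 851. The continuity-corrected formula gives 816, which goes to 894 or 902. Neither reaches 840, and both depart from the stated 776.

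**5. The margin actually present.** 840 − 776 = 64 patients.
- 64/776 = 8.2% added to the evaluable number.
- 64/840 = 7.6% loss with 776 still evaluable.

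**6. Power after loss.** Equal loss in both arms is assumed, and n is the evaluable number per arm:

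power = Φ{[0.10 × √n − 1.960 × 0.7036] / 0.7000}

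| Loss from 840 | Evaluable | Power |
|---|---|---|
| 0% | 840 | 83.1% |
| 5% (earlier trial) | 798 | 81.2% |
| 7.6% | 776 | 80.1% |
| 8.7% (1 − 1/1.095) | 767 | 79.6% |
| 9.5% | 760 | 79.2% |

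Power equals 80% at 2 × 387.34 = 774.7 evaluable, a loss of 1 − 774.7/840 = 7.8%. Taking the unpooled requirement of 770 instead, the limit is 70/840 = 8.3%. Both are below 9.5%.

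**The case against.** The strongest reply is that nothing of substance depends on this. 840 is within 1.2% of 850 and 2.1% of 858. Power falls by less than one percentage point even if 9.5% are lost, and at the only loss rate the section cites it stays above 80%. That stands, and it is why the point is minor. It does not make the percentage right.

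A second reply is that a safety margin need not mean a tolerated loss. "A safety margin of 9.5% is built in to allow for loss to follow-up" can be read as an addition to 776. This is a fair reading and the milder one: the implied loss is 8.7%, and the shortfall is 10 patients (850 against 840). It still does not give 840.

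Three stronger conclusions are tempting, and the document supports none of them:

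- **That 9.5% is the standard by which follow-up is judged.** The Sample size section says centers with poor follow-up are watched and may be withdrawn, but attaches no percentage to this. There is no basis for replacing 9.5% with a 7.6% monitoring limit either.
- **That power drops below 80% once loss passes 7.6%.** That loss preserves 776, where power is 80.1%. The 80% point is at about 7.8%.
- **That the trial is materially underpowered.** The table in the working shows otherwise.

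**Conclusion.** The stated 9.5% is wrong as written. By neither usual convention does it take 776 to 840, and nothing else in the article accounts for the gap. The margin provided is 64 patients: 8.2% of 776, or 7.6% of 840.

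At a 9.5% loss the trial would be 16 patients short of its own requirement, with power 0.8 points under target. On the milder reading it would be about 9 short (776 − 767) and 0.4 points under. Severity is minor.

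The inconsistency between the three figures needs no assumption. The power figures assume 50% against 60%, equal allocation, equal loss in both arms, and analysis of patients with an observed outcome by the uncorrected test.

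**What to change.** Keep 840 and restate the sentence in the Sample size section, for example:

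> A margin of 64 patients (8.2% of 776) allows for 7.6% loss to follow-up; at 9.5% loss, 760 would be evaluable and power would be about 79%.

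This costs one sentence. It adds no patients and leaves the recruitment target in the abstract, the analysis and the conduct of the trial unchanged. The stated tolerance becomes slightly less favorable. If covering a 9.5% loss was truly the intention, the matching total would be 858, which is 18 more patients; the small difference in power gives little reason to do that.
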